#### Study design and allocation

2.1.1

This study is a randomized, assessor-blinded, parallel-group, open-label, multicenter clinical trial. It will be conducted at two Korean medical hospitals: Kyung Hee University Hospital at Gangdong and Dongguk University Ilsan Oriental Medical Hospital. Participants who voluntarily sign the informed consent form will undergo screening examinations during their initial visit (screening visit), including interviews, vital sign measurements, questionnaire surveys, assessments with Korean medicine diagnostic devices, and laboratory tests. Eligible participants will then be enrolled. Within 2 weeks of the screening visit, participants will be randomly assigned to either the ACCORD group, which will receive YJT, PWS, or SST based on a machine learning–driven herbal response prediction algorithm, or the DISCORD group, which will be randomly assigned one of the two herbal medicines not selected by the prediction algorithm from the three options. This ACCORD vs. DISCORD design is specifically employed to validate the algorithm’s discriminative ability—that is, whether the algorithm can accurately distinguish the optimal treatment from suboptimal alternatives for an individual patient. This validation of predictive accuracy is a necessary step before evaluating clinical utility against standard care.

The machine learning algorithm employed in this trial was developed in a prior preliminary clinical study (*N* = 265) (19) (the resulting paper detailing the development methodology is currently under review; Supplementary material 1). The algorithm utilizes the XGBoost (Extreme Gradient Boosting) regressor framework. The objective of the model is a regression task: to predict the magnitude of symptom improvement (effect size) for each of the three herbal formulations (YJT, PWS, and SST). The prediction system recommends the formulation expected to yield the greatest therapeutic benefit for the individual.

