The ground truth (target variable) for model training was the observed change in the Gastrointestinal Symptom (GIS) score from baseline to 8 weeks in the preliminary study. The models were trained using comprehensive baseline data as input features. These features included demographics (e.g., age, sex, and FD duration); patient-reported outcomes and questionnaires (e.g., GIS, and various pattern identification questionnaires); data from Korean medicine diagnostic devices (e.g., tongue diagnosis system, radial pulse analyzer, and digital algometer readings); and laboratory test results (e.g., blood chemistry).

During development, the dataset was split into training (80%) and test (20%) sets for internal validation. Hyperparameter tuning was conducted using RandomizedSearchCV with 5-fold cross-validation on the training data. To mitigate overfitting due to high data dimensionality, an iterative feature selection process was employed to enhance model robustness. The final models demonstrated robust predictive accuracy on the independent test set, confirming their capability to predict treatment responses and discriminate the relative effectiveness among the herbal formulations. Detailed methodology of the algorithm development is provided in Supplementary material 1. The algorithm for prediction system employed in this trial is a locked version (v1.1) that will not be updated during the study period. The prospective validation of this locked algorithm in a new cohort is essential for evaluating its generalizability and mitigating potential biases or overfitting inherent in the preliminary training dataset.

All groups will take the assigned clinical trial medications for 8 weeks. Participants will attend clinic visits at 4-week intervals until week 8 for evaluation of clinical variables, including vital signs, questionnaire surveys, and assessments with Korean medicine diagnostic devices (heart rate variability [HRV], tongue diagnosis, pulse diagnosis, and abdominal diagnosis). In addition, telephone visits will be conducted at 2-week intervals (weeks 2 and 6) to assess whether FD-related pain or discomfort has moderately improved since the previous treatment (Figure 1). Before and after taking the herbal medicine, blood samples (at screening and week 8) and stool and saliva samples (at weeks 0 and 8) will be collected to analyze blood and fecal metabolites as well as gut and oral microbiomes. A detailed assessment schedule is provided in Table 1.

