### Sample size calculation

2.7

Participants will be randomly assigned to either the ACCORD group, which will receive YJT, PWS, or SST based on the machine learning–driven prediction, or the DISCORD group, which will not use the machine learning-based prediction for herbal assignments. Based on preliminary clinical trial results (19), the mean change in the GIS score after 8 weeks in both the ACCORD and DISCORD groups is assumed to be 2.72, with a standard deviation of 4.57. To meet this requirement, each group will require 45 participants. Considering a 10% dropout rate, the total required sample size is 100 participants. This sample size was determined for the prespecified primary comparison (ACCORD vs. pooled DISCORD) and was not inflated to power subgroup or stratified analyses, which will be considered exploratory.

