### Statistical analysis

2.8

All statistical analyses will be conducted using two-sided tests with a significance level of 5%. For continuous data, means and 95% confidence intervals will be presented, whereas categorical data will be presented as frequencies and percentages. All analyses will be performed using SAS® Version 9.4 (SAS Institute Inc., Cary, NC, United States).

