#### Statistical analysis and evaluation of efficacy endpoints

2.8.2

The primary efficacy endpoint is the between-group difference in the GIS score at week 8 (ACCORD vs. DISCORD). The primary endpoint will be analyzed using the MMRM, with treatment group and visit time as fixed factors and participant as a random factor.

The secondary efficacy endpoints include TDS, AR for dyspepsia, OTE, dyspepsia VAS, FD-QoL, Spleen Qi Deficiency Questionnaire, Stomach Qi Deficiency Questionnaire, Food Retention Questionnaire, Cold–Heat Pattern Questionnaire, and Deficiency–Excess Pattern Questionnaire. Categorical secondary variables will be analyzed using the chi-square test or Fisher’s exact test.

To address the issue of multiple comparisons for the multiple secondary efficacy endpoints, the Benjamini-Hochberg procedure (False Discovery Rate, FDR) will be applied to adjust the *p*-values. The primary endpoint will be tested at a significance level of 0.05 without adjustment. Exploratory outcomes will not be adjusted for multiplicity, and their results will be interpreted as hypothesis-generating.

Exploratory subgroup analyses (by assigned herbal formula and by DISCORD subgroup) will be performed to assess the consistency of treatment effects; these analyses are hypothesis-generating and are not powered for confirmatory inference. Effect modification will be explored using treatment-by-subgroup interaction terms within the mixed model, and results will be reported as effect estimates with 95% confidence intervals and interpreted cautiously.

For the primary outcome, missing data will be handled using the last observation carried forward (LOCF) method. In addition, multiple imputation will be applied as a sensitivity analysis to assess the robustness of results under different assumptions regarding missingness. The main analyses will be conducted on an intention-to-treat basis, with per-protocol analyses performed for comparison.

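### The algorithm predicts each participant's 8-week GIS change before allocation, but the primary model uses neither those predictions nor baseline GIS, so precision is lost without bias

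*Protocol article*

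**What the plan says.** Section 2.1.1 (Study design and allocation) describes a locked XGBoost regressor, version 1.1, whose task is "to predict the magnitude of symptom improvement (effect size) for each of the three herbal formulations (YJT, PWS, and SST". Its training target was GIS change from baseline to week 8. Its inputs are baseline data: demographics, questionnaires including GIS itself, diagnostic-device readings and laboratory results. On performance, the section states: "The final models demonstrated robust predictive accuracy on the independent test set". It gives no R², correlation or error.

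Section 2.1.2 (Randomization and blinding) stratifies by herbal medicine and gives DISCORD patients one of the two formulas that the algorithm did not choose.

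Section 2.8.2 defines the primary endpoint as the between-group difference in GIS score at week 8, analysed by an MMRM "with treatment group and visit time as fixed factors and participant as a random factor". Section 2.8.1 gives the only route for a covariate into that model: a statistically significant baseline difference between groups.

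Section 2.7 says "the mean change in the GIS score after 8 weeks in both the ACCORD and DISCORD groups is assumed to be 2.72". It takes the SD as 4.57 and concludes that "each group will require 45 participants", or 100 in total after 10% dropout.

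**The concern.** Section 2.1.2 says that the DISCORD group will not use the algorithm, but its own example excludes the algorithm's choice from that group. The algorithm must therefore be run for everyone before allocation. The mean of a participant's three predicted changes is fixed before randomisation, comes from a model trained on other patients, does not depend on the arm, and concerns the primary scale and time point.

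The stated model leaves this out, and baseline GIS as well. The rule in section 2.8.1 does not repair that, because it selects covariates on chance imbalance rather than prognostic value. GIS variation that was predictable at baseline then widens the confidence interval of the primary comparison, in a trial whose sample size appears to leave no reserve of power.

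This is not a detail left to an unseen analysis plan, since the article itself lists the model terms and the covariate rule.

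**Working it through.** **Inputs.** From the article: "two-sided tests with a significance level of 5" percent; SD 4.57; 45 evaluable per group; 1:1 allocation; 10% dropout. Two readings are inferred. The figure 2.72 is taken as the between-group difference, although section 2.7 gives it as the mean change in both groups. Power is taken as 80%, because none is stated.

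**Reproducing the plan's figure.** n = 2 × [4.57 × (1.960 + 0.842) / 2.72]² = 44.3, rounded up to 45 per group. Then 45 / 0.90 = 50 per group, or 100 in total. The figure reproduces and takes no credit for covariates. Power at 45 per group is 80.6% by the normal approximation and 79.7% by the t distribution.

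**Standard error for change, no covariates.** 4.57 × √(2/45) = 0.963.

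**Adding covariates.** With k covariates explaining a share R² of the variance of change, SE ≈ 0.963 × √(1 − R²) × √(1 + k/(90 − k − 3)). The last factor is the price of estimating the covariates: 1.0058 for k = 1 and 1.0117 for k = 2. Baseline GIS is assumed to explain 15%, and the score's extra share is varied. Power uses the noncentral t distribution.

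| Model | Total R² | SE | Power |
|---|---|---|---|
| Baseline GIS only (k = 1) | 0.15 | 0.893 | 85% |
| + score, adds 0% (k = 2) | 0.15 | 0.899 | 85% |
| + score, adds 5% | 0.20 | 0.872 | 87% |
| + score, adds 10% | 0.25 | 0.844 | 89% |
| + score, adds 20% | 0.35 | 0.786 | 93% |

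The cost of a worthless score is 0.899 / 0.893, about 0.6% on the SE. The last three rows correspond to (0.893/SE)² = 1.05, 1.12 and 1.29 times the patients. A simulation of 3,000 trials per setting agrees: SE 0.89 with baseline GIS, then 0.867, 0.842 and 0.785. In it the rejection rate under no effect was 0.046 to 0.053 with the score in the model.

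**Why baseline GIS must come with the score.** The algorithm predicts change, but the endpoint is the week-8 score. A second simulation (4,000 trials, 45 per arm) assumed baseline SD 6, correlation 0.4 between baseline and change, and 0.6 between baseline and the score. With a correlation of 0.5 between score and change, the SE on the week-8 score was:

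- no covariate: 1.25
- predicted change alone: 1.22
- baseline GIS alone: 0.88
- both: 0.83

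Under these assumptions the score's increment in R² over baseline is (0.16 + 0.25 − 2 × 0.4 × 0.5 × 0.6)/(1 − 0.36) − 0.16 = 0.106. For correlations of 0.2, 0.4 and 0.6 the same formula gives 0.003, 0.04 and 0.20. The range of 0 to 20% in the table therefore corresponds to a score that correlates with change at roughly 0.2 to 0.6.

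**Why not the prediction for the formula received.** That value depends on the arm. In the same simulation, a covariate shifted by arm in this way pulled the estimate from about 2.7 down to between 1.1 and 2.2.

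**The case against.** The strongest reply is that nothing here is wrong: the unadjusted randomised comparison is valid, and a machine-learning prognostic covariate is an enhancement. It is true that no bias is involved. But the article does fix the model terms and the covariate rule, and it fixes them in a way that discards information already collected.

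The second reply is that the gain is undocumented. This stands. The article's accuracy claim is qualitative and rests on a 20% split of 265 patients, about 53 across three formulas. The same section says prospective validation is needed because of possible overfitting. GIS is an algorithm input, so part of the score repeats baseline GIS. The system is designed to rank formulas within a patient, and averaging the three predictions sets that contrast aside; whether the average is prognostic is not reported. The true increment could be near zero.

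The third reply concerns the endpoint. A reader might infer that the model as written has an SE of 0.96 and that the score should be credited with the whole improvement from there. The documents do not support that. The value 0.96 rests on the SD of change, whereas section 2.8.2 names the week-8 score, and much of the improvement comes from baseline GIS.

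Finally, these are single-time-point calculations without the stratum or the week-4 data. They indicate direction and rough size, not the exact performance of the planned MMRM.

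**Conclusion.** The point holds as a loss of precision that can be avoided at almost no cost. The primary model omits baseline GIS and an arm-independent prediction of the primary outcome that must exist for every participant before allocation.

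The score's own contribution is only what it adds to baseline GIS. For an assumed extra R² of 5 to 20%, that is a fall in SE from about 0.89 to between 0.87 and 0.78 to 0.79, and a rise in power from about 85% to between 87 and 93%. At the low end the gain is marginal. At zero there is a loss of about 0.6% in SE. These figures rest on SD 4.57, a between-group difference of 2.72, 45 evaluable per arm and the assumed 15% for baseline GIS.

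A reader might infer that the planned estimate is biased or that the trial is underpowered. Neither follows: the unadjusted comparison remains valid, and the stated sample size reproduces at about 80% power on the inferred readings.

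**What to change.** Have the randomisation system store the three version 1.1 predictions at allocation. In section 2.8.2, prespecify these fixed covariates in the primary MMRM:

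- baseline GIS and its interaction with visit (required, because the score predicts change and the endpoint is the week-8 value);
- the mean of the three predicted GIS changes and its interaction with visit;
- the recommended-formula stratum.

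State that the prediction for the formula actually received will not be used as a covariate. Let this prespecified list replace the significance-test rule in section 2.8.1, and fix it before any outcome data are seen.

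The cost is a sentence or two of text and storage of values the system already computes. No extra patients, visits or measurements are needed. The statistical price of the score is one or two degrees of freedom.

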**Figure 1 fig1:**
[figure not shown]
Flowchart of the trial intervention. ML, machine learning; YJT, *Yijung-tang*; PWS, *Pyeongwi-san*; SST, *Shihosogan-tang*; GIS, gastrointestinal symptom.

**Table 1 tab1:** Clinical study schedule.

Assessment	Visit 1 (screening)	Visit 2 (baseline, week 0)	Visit 3 (week 2)	Visit 4 (week 4)	Visit 5 (week 6)	Visit 6 (week 8)
Written consent						
Demographic/medical history survey	●					
Physical measurements	●					
Vital sign measurements	●	●		●		●
Blood test	●					
Confirmation of inclusion / exclusion criteria	●					●
Random allocation		●				
Concomitant medications and adverse reaction confirmation		●	●	●	●	●
Gastrointestinal Symptom Score	●			●		●
Total Dyspepsia Symptom Score	●			●		●
Adequate relief of dyspepsia			●	●	●	●
Overall treatment effect				●		●
Dyspepsia Visual Analog Scale	●			●		●
Functional dyspepsia–related quality of life	●			●		●
Spleen Qi Deficiency Questionnaire	●			●		●
Stomach Qi Deficiency Questionnaire	●			●		●
Food Retention Questionnaire	●			●		●
Cold–Heat Pattern Questionnaire	●			●		●
Deficiency–Excess Pattern Questionnaire	●			●		●
Standard Tool for Pattern Identification of FD	●					
Korean medicine diagnosis (interview, tongue, pulse, abdominal)	●			●		●
Clinical trial medication prescription and administration education		●		●		
Clinical trial medication returns and compliance check				●		●
Stool kit and meal record sheet provision	●			●		
Stool sample collection, meal record sheet confirmation, and saliva sample collection		●				●
Confirmation of clinical study completion						●

#### Randomization and blinding

2.1.2

Participants will be divided into the ACCORD group, assigned herbal medication by the machine learning-based prediction algorithm, and the DISCORD group, which will not use the prediction algorithm. For example, if the prediction algorithm assigns YJT, the group receiving YJT will constitute the ACCORD group, whereas those receiving PWS or SST will constitute the DISCORD groups. Randomization will be stratified by each herbal medicine using block randomization to minimize bias before the clinical trial begins. For each stratification factor, the group allocation ratio will be 1:1 (ACCORD: DISCORD), with block sizes of 4 and 8. The DISCORD group will then be divided into two subgroups, excluding the optimal herbal medicine per the prediction algorithm, and randomly assigned, resulting in a 2:1:1 allocation (ACCORD: DISCORD_1: DISCORD_2). To prevent bias toward a specific herbal medicine, the maximum number of participants assigned to any single herbal medicine will be capped at 48. Any additional participants for that medicine will be excluded during screening.

Randomization tables will be generated using SAS® Version 9.4 (SAS Institute Inc., Cary, NC, United States) by a medical statistician independent of the trial interventions and assessments. The randomization list will allow for the registration of 50 participants per institution. The randomization system will be managed by a medical statistician, independent of the trial, serving as the system administrator. Investigators will be able to access participant identification codes and group allocation information only with administrator approval. To ensure allocation concealment, a centralized, web-based randomization system will be utilized. This system will be managed by the independent medical statistician serving as the administrator. Once a participant is confirmed eligible and enrolled, the investigator will access the web-based system, which will then reveal the participant’s unique identification code and group allocation. The system ensures that the allocation sequence remains concealed until the point of assignment. Evaluation of participant outcomes will be conducted by staff who will not prescribe medications or access medical records and case report forms. Evaluators will ask only the questions necessary for assessment and will remain blinded to participant group assignments. These procedures, including centralized randomization managed by an independent statistician, allocation concealment, and assessor blinding, are implemented to minimize potential selection and assessment bias throughout the trial.

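### The primary model leaves out hospital although the randomisation list provides 50 places at each of two hospitals; a prespecified hospital term would cost one degree of freedom and could only modestly help precision

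*Protocol article*

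**What the plan says.** The trial runs at two hospitals (protocol article, section 2.1.1). On the randomisation, section 2.1.2 says "Randomization will be stratified by each herbal medicine using block randomization", and that within each stratum "the group allocation ratio will be 1:1 (ACCORD: DISCORD), with block sizes of 4 and 8". It names no other stratification factor. The same section adds: "The randomization list will allow for the registration of 50 participants per institution". It does not say whether the blocks are built within each hospital.

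Section 2.8.2 specifies the primary analysis as an MMRM "with treatment group and visit time as fixed factors and participant as a random factor". Section 2.8.1 gives the only stated route by which a further variable can enter that model: a statistically significant baseline difference between the groups.

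**The concern.** The list is described by hospital, yet hospital is not in the model that gives the only confirmatory test. The covariate rule does not repair this. If the list balances the arms within hospital, hospital will almost never differ significantly between arms. If it does not, hospital would pass a 5% screen only about one time in twenty, by chance. Whether a variable is imbalanced also says nothing about whether it predicts the GIS score, which is what matters for precision.

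What is at stake is precision. If patients at the two hospitals differ in GIS outcome, the part of the variance that hospital explains is counted as noise, although every participant's hospital is known. The sample size leaves little slack: 45 per group corresponds to about 80% power.

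**Working it through.** **Inputs from the article.** Two-sided 5% level (2.8). From 2.7: "DISCORD groups is assumed to be 2.72, with a standard deviation of 4.57", "To meet this requirement, each group will require 45 participants" and "Considering a 10% dropout rate, the total required sample size is 100 participants".

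**Assumptions.** Power is not stated; 80% is assumed. The value 2.72 is read as the between-group difference, because that reading returns 45. The hospital gap D in GIS is not given; 0 to 4 points is shown. The hospitals are taken as equal in size. A two-arm comparison at week 8 stands in for the MMRM.

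**1. The plan's own figure.** n per group = 2 × (1.960 + 0.842)² × 4.57² / 2.72² = 2 × 7.849 × 20.885 / 7.398 = 44.3, rounded up to 45. With 10% dropout, 45 / 0.90 = 50 per group, 100 in total. Both stated figures reproduce.

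**2. Effect of omitting hospital.** With two equal hospitals that differ by D, omission adds D²/4 to the variance. With 4.57 taken as the within-hospital SD:

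- SE with hospital in the model = 4.57 × √(2/45) = 0.963
- SE without it = 0.963 × √(1 + D²/(4 × 4.57²))
- Power ≈ Φ(2.72/SE − 1.96)

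| D (assumed) | SE without hospital | Increase | Power without | Power with |
|---|---|---|---|---|
| 0 | 0.963 | 0% | 80.6% | 80.6% |
| 1 | 0.969 | 0.6% | 80.1% | 80.6% |
| 2 | 0.986 | 2.4% | 78.8% | 80.6% |
| 2.72 | 1.005 | 4.3% | 77.2% | 80.6% |
| 4 | 1.052 | 9.2% | 73.4% | 80.6% |

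**3. The other reading of the SD.** If 4.57 already contains the hospital difference, omission costs nothing against the planned 80.6%. Adding hospital then raises power to 81.1% (D = 1), 82.5% (D = 2), 84.1% (D = 2.72) or 88.1% (D = 4).

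**4. Is the reported SE right?** This depends on how the list is built. It was simulated with 8,000 runs per setting, 90 participants, and blocks of 4 and 8 either within hospital and herbal medicine or within herbal medicine only. The figures are for the model without hospital; true SE means the spread of the estimates across runs.

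| D | Blocked within hospital: reported / true SE | Type I error | Herbal medicine only: reported / true SE | Type I error |
|---|---|---|---|---|
| 2 | 0.984 / 0.965 | 4.4% | 0.983 / 0.984 | 4.8% |
| 2.72 | 1.004 / 0.979 | 4.5% | 1.004 / 1.003 | 4.9% |
| 4 | 1.051 / 0.981 | 3.5% | 1.050 / 1.048 | 4.7% |

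The simulation error on a 5% rate is √(0.05 × 0.95 / 8,000) = 0.24 percentage points, so the small differences between adjacent rows should not be over-read. With D = 0, leaving hospital out makes no material difference under either scheme.

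**The case against.** A reader might infer that the primary standard error is simply too wide. The documents do not support that as a flat statement. It needs two things together: blocking within hospital, and a real hospital difference in GIS. The article establishes neither. The sentence about 50 per institution may describe list capacity or a recruitment quota, and the only named stratum is herbal medicine. With herbal-medicine strata alone, the simulated standard error is right and type I error stays near 5%; what is lost is precision.

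A reader might also infer that the hospitals have separate raters and recruitment areas and so must differ. The article does not say how evaluators are divided. The one device difference between sites that it states, the heart rate variability analyser in 2.5.4, concerns an exploratory measure. Nor is there a false-positive risk: any miscalibration is in the conservative direction.

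The size also deserves caution. The SD of 4.57 is given for the 8-week change, so D is a gap on that scale, and a gap of 4 points would exceed the 2.72 used as the treatment difference. The lower rows of the table are the more reasonable guide.

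All of this stands. Less persuasive is the argument that a centre term may be left to an unseen analysis plan. Such a plan may include one, but the article states both the model terms and the rule for adding covariates, and together they leave hospital out. It is also fair that the plainer mismatch is the absence of herbal medicine, the named stratum, from the model. That is a reason to add both terms.

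**Conclusion.** The point holds as a low-cost improvement in precision, not as an error that invalidates the primary test. As stated, the model and the covariate rule exclude hospital. The cost depends on an undocumented hospital difference: zero with no gap, and a standard error larger by 0.6% to 4.3% for assumed gaps of 1 to 2.72 points. If 4.57 is the within-hospital SD, power falls from 80.6% to between 80.1% and 77.2% over that range. If 4.57 already includes hospital variation, planned power is not reduced and the term is a gain.

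Only if the blocks run within hospital and the hospitals differ does the reported standard error exceed the true one, with type I error of about 4.4% at a 2-point gap. The recommendation does not depend on which reading of the list is correct: when the hospitals differ the term helps under both, and when they do not it is close to neutral.

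**What to change.** In section 2.8.2, add hospital (two levels) as a prespecified fixed effect in the primary MMRM, alongside the named herbal-medicine stratum. Include both whatever the 2.8.1 screen shows. Use the same terms in any mixed models for continuous secondary endpoints.

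In section 2.1.2, state whether the blocks run within hospital. This should describe the scheme already in place; the randomisation itself need not change.

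Cost: a few lines of wording and one degree of freedom for hospital (the three-level herbal-medicine stratum uses two more). No new data or participants are needed. The wording should be settled before outcome data are seen by group.
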